#### The quantity of self-reported data using MyCanRisk.

The amount of information completed for non-family history risk factors alongside the number of family members reported in the pedigree will be summarised using descriptive statistics. Chi-square tests will be used to assess differences in the amount of information provided between demographic subgroups.

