## Study outcomes and measures

The study aims to generate data on the following outcomes:

Uptake of multifactorial breast cancer risk assessment, including the proportion of those invited who consent and the proportion of those invited who complete the breast cancer risk assessment, with or without the inclusion of the polygenic risk score.Distribution of breast cancer risk, including the proportion of women who consent who are at moderate or high risk on the initial CanRisk assessment in general practice (with or without the PGS) and those at moderate or high-risk following assessment in secondary/tertiary care.Proportion of women at moderate or high risk of breast cancer. The proportion of registered women aged 40–48 years at the start of the study at participating practices who are at moderate or high risk of breast cancer after assessment in secondary/tertiary care will be compared with the proportion of women aged 40–48 years at moderate or high risk of breast cancer after referral to secondary/tertiary care at non-participating practices across Cambridgeshire and Peterborough during the same time period, and also compared with the proportion of registered women aged 40–48 years at participating practices in the 12 months prior to the study.Uptake of risk-reducing interventions, including the proportion of those at moderate or high risk who attend for a GP appointment, are referred to secondary/tertiary care, and take up enhanced screening and/or preventative medication.Completeness of risk factor information collected through MyCanRisk, including the presence of information completed for non-family history risk factors (e.g., height, weight, alcohol, women’s health) and the number of family members included in the pedigree.Change in psychological and behaviour measures (Table 2) following multifactorial breast cancer risk assessment at one month, three months, and six months after receiving the risk estimate.Acceptability of the pathway of proactive multifactorial risk assessment within general practice to women and GPs, including response rates and completion of questionnaires and the willingness for practices to take part.Costs and workload associated with delivery of proactive multifactorial risk assessment.

**Table 2 pone.0336902.t002:** Assessments.

Construct	Baseline	1 month	3 months	6 months

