### Sample size

Based on an uptake of 16% in the only study in the UK that invited women to complete a breast cancer risk assessment [35], we estimate that to recruit 1,000 women we need to invite approximately 5,000 women from across the GP practices.

Based on distributions of known risk factors in the UK, we estimate that approximately 17% (170) of those 1,000 women will be at above population-level risk [1]. This will allow us to estimate:

the proportion of eligible women in each practice who consent to take part in the study with an accuracy of +/- 1.1% (width of the 95% CI) based on an estimate of 20%the proportion of eligible women in each practice who consent who complete the risk assessment with an accuracy of +/- 2.5% based on an estimate of 80%the proportion of women who consent who are at moderate or high risk on initial CanRisk assessment in general practice with an accuracy of +/- 2.5% based on an estimate of 17%the proportion of those at moderate or high risk who attend for an appointment with a GP and who are referred to secondary/tertiary care with an accuracy of +/- 5.7% based on an estimate of 80%

Allowing for a 40% loss to follow-up, 1,000 participants will allow us to detect a change in anxiety or worry of 0.5 SD or greater at each time point at p < 0.05 and 90% power in both women at population level risk and in the subgroup identified at moderate or high risk. 1,000 participants will also allow us to detect an estimated increase in the proportion of registered women identified at moderate and high risk through proactive multifactorial risk assessment across all the participating practices compared with the 12 months prior to the study with a 95% confidence interval of +/- 0.005 (5 per 1,000 registered women).

Together with data on the acceptability of the proactive multifactorial breast cancer risk assessment, the following progression criteria will be evaluated to judge whether a subsequent full trial of proactive multifactorial breast cancer risk assessment would be feasible: 16% uptake into the study; 60% response to follow-up questionnaires; 80% of women receiving their breast cancer risk and offered subsequent risk management advice/referral. If any of those criteria are not met, we will use the data from the process evaluation to adapt the approach for subsequent feasibility and/or pilot studies before consider progressing to a subsequent full trial.

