#### Uptake of breast cancer risk assessment.

Logistic regression will be used to assess the participant level characteristics associated with completion of the risk assessment amongst those consenting to the study, reporting both unadjusted and adjusted odds ratios (OR) with 95% confidence intervals. Chi-squared tests will be used to compare the proportions of those invited who take up the offer of breast cancer risk assessment between demographic subgroups using aggregate data from each participating practice. Test significant at p < 0.05 will be presented as statistically significant.

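### The number of relatives in the MyCanRisk pedigree is a count, but the only test named for subgroup differences is chi-square, which needs it cut into categories

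*Protocol article*

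**What the plan says.** The outcome list (protocol article, Study outcomes and measures) gives completeness of MyCanRisk data two parts. The first is "the presence of information completed for non-family history risk factors", with height, weight, alcohol and women's health as examples; this is naturally yes or no for each item. The second is "the number of family members included in the pedigree", which is a count.

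The analysis paragraph (The quantity of self-reported data using MyCanRisk) takes the two together: "The amount of information completed for non-family history risk factors alongside the number of family members reported in the pedigree". Both receive a descriptive summary. The paragraph then names one test: "Chi-square tests will be used to assess differences in the amount of information provided between demographic subgroups". It gives no categories or cut-points for the count, and no power, effect size or standard deviation for this comparison.

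Elsewhere the article treats numeric and categorical variables separately. Quantitative data analysis prescribes means with SDs or medians with interquartile ranges for continuous variables, and numbers with percentages for categorical ones. The uptake paragraph uses chi-square for a proportion, where it fits. The psychological outcomes are analysed as continuous by analysis of covariance.

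**The concern.** Pedigree size is the one numeric outcome in the article whose only named test is for categories. An analyst who follows the text must group the number of relatives. Three things follow.

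- Information within each group is discarded, so a real difference between subgroups is more likely to be missed.
- With three or more groups, the test does not use the fact that they are ordered.
- The result is at best a difference in the proportion above some cut. It is not a difference or ratio in the number of relatives, which is the quantity of interest.

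The practical question is whether some demographic groups enter smaller pedigrees. CanRisk needs a detailed family history for its calculation (Breast cancer risk assessment), so the answer is useful for feasibility even though no decision rule depends on it.

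**Working it through.** The plan states no power for this comparison, so there is no figure of its own to reproduce. The check asks how much power is lost when the same count is grouped.

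**Inputs from the article**
- Participants: 1,000 ("to recruit 1,000 women we need to invite approximately 5,000 women").
- Completion of the risk assessment: 80%. The stated precision confirms the base of 1,000: 1.96 × √(0.8 × 0.2 / 1,000) = 2.48%, against the stated ±2.5%.
- Women with data: 0.80 × 1,000 = 800.
- Significance level: 0.05, from "Test significant at p < 0.05 will be presented as statistically significant". This stands in the uptake paragraph and is assumed to apply here, two-sided.

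**Inputs assumed, because the documents give none**
- The distribution of pedigree size, the subgroup split, the cut-points and the size of the difference.

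**1. Closed form: normal data, two groups of 400, median split**
- Difference at which a t-test has 80% power: d = (1.960 + 0.842) × √(2/400) = 0.198 SD.
- Proportions above the common median: Φ(+0.099) = 0.539 and Φ(−0.099) = 0.461, a difference of 0.079.
- Standard error: √(2 × 0.25 / 400) = 0.0354, so z = 0.079 / 0.0354 = 2.23.
- Chi-square power: Φ(2.23 − 1.96) = 60.7%, a loss of 19.3 percentage points.

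The same calculation for other settings, with equal groups and k equal-sized categories (noncentral chi-square on k − 1 degrees of freedom), gives:

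| t-test power | Loss, median split | Loss, tertiles | Loss, quartiles | Loss, 8 categories |
|---|---|---|---|---|
| 80% | 19.3 | 20.1 | 23.0 | 33.7 |
| 90% | 16.7 | 16.7 | 19.0 | 29.5 |
| 95% | 13.1 | 12.6 | 14.3 | 23.4 |

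**2. Simulated counts: negative binomial, mean 15, k = 4, N = 800, 10% fewer relatives in one subgroup**
- Variance = 15 + 15²/4 = 71.25, so SD = 8.4. The difference is 1.5 relatives.

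| Subgroup split | Median-split chi-square | Quartile chi-square | Wilcoxon | Wilcoxon gain |
|---|---|---|---|---|
| 50/50 | 55% | 52% | 70% | 15 to 18 points |
| 25/75 | 43% | 38% | 58% | 15 to 20 points |

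With the mean between 15 and 20 and k between 4 and 10, the Wilcoxon gain stays at roughly 11 to 20 points. With no true difference, all the tests reject about 5% of the time, so the cost is in power and not in false positives.

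**3. Other assumptions**
- Counts with mean/SD of 12/6 or 20/8, with the difference set so that a t-test has about 80% or 90% power, in 2 to 4 categories: chi-square is about 10 to 20 points below Wilcoxon and about 5 to 16 below the t-test.
- Every distinct count as its own table column, same settings: about 40 to 62 points below the t-test.
- Normal data, equal groups, an uneven 25/75 cut of the count: a loss of 20 to 26 points.

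The direction is the same throughout. The size is not.

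**4. The other outcome**
For completion of a single item the data are already binary, so nothing is discarded. With two groups of 400, chi-square has 77% power for 95% against 90% completion, and 90.5% for 90% against 82%.

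**The case against.** The strongest objection is that the chi-square sentence can be read as meant for the risk-factor items, where it fits. The outcome list defines that part as presence of information and no item-count score is defined anywhere. This stands. A reader might infer that chi-square is wrong for the whole MyCanRisk comparison, and the documents do not support that. The looser word for amount in the analysis paragraph leaves an item count possible but does not create one. The sentence does, however, follow directly on one that names both outcomes, and no other test is given for pedigree size.

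Second, a reader might take the power loss as a fixed property of the plan. It is not: mean, dispersion, split, cut and difference are all assumed, and the plan makes no power claim here that could fail.

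Third, a condensed article may leave cut-points to a fuller document that is not shown. That is fair, and their absence is not counted as a defect. The point is that the test which is named requires them.

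Fourth, the objective on MyCanRisk asks only how much data are collected, and the descriptive summary answers that. The subgroup comparison feeds none of the three progression criteria (uptake, questionnaire response, receipt of risk and advice). This also stands, and it limits the weight of the point.

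Finally, fewer relatives may partly mean a smaller family and not incomplete reporting. No test on the count, grouped or full, separates the two.

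**Conclusion.** The point holds for pedigree size only. The single test named does not suit a count: it requires grouping, ignores the order of the groups and gives no effect in relatives reported. Assuming 800 women, negative binomial counts with mean 15 to 20 and k = 4 to 10, and 10% fewer relatives in one subgroup, a median-split or quartile chi-square gives up roughly 11 to 20 percentage points of power against a Wilcoxon test. None of the distributional inputs comes from the documents, and the other settings examined gave losses from about 5 points to well over 20. For item-by-item completion there is no loss. This is a minor improvement to a secondary comparison in a feasibility study. The study's main conclusions and its progression decision are unaffected.

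**What to change.** Replace the one chi-square sentence with wording to this effect:

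- Completion of each non-family-history risk-factor item is compared between demographic subgroups with chi-square tests.
- The number of relatives in the pedigree is compared on the full count, either with Wilcoxon (two subgroups) or Kruskal-Wallis (more than two) tests, or with negative binomial regression reporting ratios with 95% confidence intervals. The regression is the better choice if an effect size is wanted. An item count is handled in the same way, only if such a score is used.
- A lower count is interpreted with the caution that it may reflect true family size as well as incomplete reporting.

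The cost is a sentence or two of analysis wording, with no new data and no change to sample size or conduct. It is best settled before the MyCanRisk data are examined by subgroup.

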#### Psychological and behavioural impact of multifactorial breast cancer risk assessment.

For continuous outcomes (anxiety, worry, risk perception, recall of risk information, and intentions) analysis of covariance will be used to calculate change at each follow-up within each risk group, adjusting for clustering between each GP practice. Any differences between the risk groups on analysis of covariance will be tested using an F-test, followed by estimation of the comparison between those at near population level risk and those at moderate or high risk based on the CanRisk assessment. All models will be adjusted for age, ethnicity, education level, deprivation, baseline EQ-5D and general practice. The size of the change between groups will be interpreted by comparison with the standard deviation (SD), with the criteria for clinically relevant change being a change of 0.5 SD [29]. We will also test for interactions between the risk groups and age, family history of breast cancer, numeracy, beliefs about breast cancer, time orientation, intolerance of uncertainty and responding “not anxious or depressed” versus “slightly/moderately/severely or extremely anxious or depressed” on EQ-5D at baseline. Analyses will be repeated within the subgroups where the p value for interaction is < 0.05.

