**Moderators**				
Numeracy [28]	•			
Health literacy [29]	•			
Beliefs about breast cancer [30]	•			
Time orientation [31]	•			
Intolerance of uncertainty [32]	•			

Table 2 specifies all measures, instruments and data collection points (baseline and at 1, 3 and 6 months after receiving the risk assessment results). All outcomes will be measured by self-report and include risk perception, psychological impacts of the risk assessment, lifestyle and behaviour, and actions taken following the risk assessment. Risk perception will be assessed using questions about absolute and comparative risk, risk conviction and recall of risk. Psychological measures include cancer-related worry, anxiety and quality of life using the Lerman cancer worry scale [21], the short-form of the state scale of the Spielberger State Trait Anxiety Inventory (STAI) [22] and the EQ-5D-5L [23, 24] respectively. These have been chosen as the Lerman cancer worry scale and short-form STAI have been widely used in the literature and so will allow comparison with other studies, and the EQ-5D-5L is the recommended measure for use in economic analyses by NICE [25]. We will also collect data on: motivations and concerns regarding participation in the study using multiple choice questions and short open text boxes questions; the acceptability of the study using 5-point Likert scale questions [26]; the impact of cancer risk assessment using the MICRA scale [27]; satisfaction with the test using 5-point Likert scale; questions assessing the degree of satisfaction with the multifactorial cancer risk assessment; views on the risk information using 5-point Likert scale questions assessing the information in the CanRisk report; views on the GP consultation, including assessing the usefulness of the consultation and whether the appointment clarified understanding of breast cancer risk. Additionally, patients who agree to have their appointment recorded will receive an optional survey immediately after their GP consultation exploring their experience of the appointment. Attitudes towards risk management options (i.e., earlier or more frequent screening, medication and surgery) will also be measured via standardised scales and multiple-choice questions reviewed by patient and public partners. Lifestyle and behavioural data will be collected through multiple choice questions; these will include question about current behaviour regarding breast self-examination, intention to attend screening, change in behaviour (i.e., weight, alcohol consumption and exercise) and healthcare utilisation (i.e., number and type of contact) specifically focusing on breast health in the six months prior to baseline and six months after baseline. Data on actions following the risk assessment will only be collected for women found to be at increased risk and if they have attended the GP appointment. Actions measured will include multiple choice questions about the attendance at the GP appointment (or intention if not done) as part of the study and uptake (or intention if not done) of risk reduction strategies (i.e., earlier or more frequent screening, medication and surgery). We will also collect data on numeracy [28], health literacy [29], beliefs about breast cancer [30], time orientation [31], and intolerance of uncertainty [32]. These will be considered as moderators for the measures above that will help test interactions between variables in the study.

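### ANCOVA at each follow-up leaves scores from other visits unused when 40% loss is expected, so within-group change in anxiety and worry is open to bias of unknown direction

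*Protocol article*

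**What the plan says.** The Analysis section of the protocol article, under psychological and behavioural impact, fixes the method for anxiety, worry, risk perception, recall and intentions: "analysis of covariance will be used to calculate change at each follow-up within each risk group", with allowance for clustering by practice. The covariates are also fixed: "All models will be adjusted for age, ethnicity, education level, deprivation, baseline EQ-5D and general practice". No score from another follow-up is among them. An F-test across risk groups follows, then a comparison of near-population with moderate or high risk. The size of the difference in change between groups is to be read against the SD, "the criteria for clinically relevant change being a change of 0.5 SD".

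The outcomes are collected at baseline and at 1, 3 and 6 months after the risk result (Table 2 and Data collection).

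The Sample size section begins its power statement with "Allowing for a 40% loss to follow-up" and states, for each risk group, what 1,000 participants can achieve: "detect a change in anxiety or worry of 0.5 SD or greater at each time point at p < 0.05 and 90% power". It also sets a 60% questionnaire response as a progression criterion.

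**The concern.** One objective is to quantify the psychological impact of the risk assessment. An ANCOVA at a given visit can use only women who answered at that visit. A woman who replies at 1 month but not at 6 months counts at 1 month, but her 1-month score does nothing for the 6-month estimate, although it is recorded and may help to explain why she stopped replying.

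The expected loss is large and enters the power statement, but no part of the analysis that the article describes. The study could meet its own response criterion with 40% of scores missing. If reply depends on how a woman reacted to her result, the 3- and 6-month changes describe those still responding rather than all women who received a result.

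**Working it through.** **Inputs from the protocol article.** 1,000 women; "we estimate that approximately 17% (170) of those 1,000 women will be at above population-level risk"; 40% loss; 0.5 SD; p < 0.05; 90% power. Responders: 1,000 × 0.6 = 600, of whom 170 × 0.6 = 102 are at moderate or high risk and 830 × 0.6 = 498 at population-level risk.

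**Assumptions, because the article gives no figure.** A two-sided test; the correlation ρ between visits; the relation between non-response and anxiety; and that the ANCOVA adjusts for the baseline value of the outcome, as is usual.

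**Step 1: the plan's power figure.** For a within-group change, SD of change = SD × √(2(1 − ρ)), and n = [SD of change × (1.960 + 1.282) / 0.5]².
- ρ = 0: SD of change = 1.414, n = 85, or 85 / 0.6 = 142 before loss. Power with 102 responders is 94%.
- ρ = 0.5: SD of change = 1, n = 43, or 43 / 0.6 = 72 before loss. Power with 102 is over 99%.
- With 498 responders power is about 100%. The between-group contrast (102 v 498) has 99.6% power.

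The stated 90% therefore holds. The issue is bias, not power.

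**Step 2: general size of the bias.** Responder mean − full mean = −0.40 × δ, where δ is the mean change in non-responders minus that in responders. For δ = 0.25, 0.5 and 1.0 SD the responder mean is too low by 0.10, 0.20 and 0.40 SD. A negative δ gives the same errors upward.

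**Step 3: loss that depends on an observed score.** Simulation with baseline, 1-month and 6-month scores, equal correlations of 0.5 to 0.7, true change 0.50 SD, 40% missing at 6 months, non-response logistic in the standardised 1-month change, and every 1-month score present:

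| Dropout odds ratio per SD | Baseline-adjusted ANCOVA | Also using the 1-month score |
|---|---|---|
| 1.25 | about 0.48 | 0.49–0.50 |
| 1.5 | about 0.46 | 0.49–0.50 |
| 2 | about 0.43–0.44 | 0.49–0.50 |

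The shortfall is 0.02 to 0.07 SD, or 4% to 14% of 0.50.

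**Step 4: what if 1-month scores are missing too?** Odds ratio 1.5, correlation 0.5, 40% missing at 6 months, and women missing at 1 month also missing later:

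| Missing at 1 month | ANCOVA | All available scores |
|---|---|---|
| 0% | 0.46 | 0.50 |
| 20% | 0.46 | 0.48 |
| 30% | 0.46 | 0.47 |
| 40% | 0.46 | 0.46 |

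Recovery falls from full, to about half ((0.48 − 0.46) / (0.50 − 0.46)), to none.

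**Step 5: loss that depends on the unobserved current score** (correlation 0.5, earlier score complete). At odds ratios 1.5, 2 and 3, ANCOVA gives 0.38, 0.31 and 0.22, and the analysis with the earlier score gives 0.39, 0.33 and 0.25. At an odds ratio of 0.5, where calmer women stop replying, ANCOVA gives 0.69. With unrelated non-response both give 0.50.

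**Step 6: the between-group contrast**, with non-response on the 1-month change and a true contrast of 0.50 SD. With the same dropout mechanism in both groups the contrast stays at 0.48 to 0.50 SD. If distress drives dropout only in the moderate or high-risk group, it falls to about 0.45 (odds ratio 1.5) or 0.42 to 0.43 (odds ratio 2).

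**The case against.** The strongest reply is that the article does not speak of separate models or complete cases, and that imputation and sensitivity analyses commonly sit in an analysis plan that is not shown. That is right, and the absence of a missing-data section is not the point. What stands is that the article names a model, lists its covariates and leaves the other follow-ups out of both.

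Three stronger readings are tempting, and the documents support none of them.
- A reader might infer that impact **is** understated. Nothing in the article says who stops replying or why, and Step 5 shows overstatement under the opposite pattern.
- A reader might infer that a true 0.5 SD rise would be declared not clinically relevant. The Analysis section applies that criterion to the change between groups, where similar dropout largely cancels. The Sample size section uses 0.5 SD within groups only as a detectable effect. Placing the truth exactly on the threshold also makes any downward shift cross it.
- A reader might infer that a repeated-measures model removes the problem. Steps 4 and 5 show that it recovers little or nothing when women leave before any follow-up or because of distress not yet recorded.

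It is also fair to say that this is a feasibility study, that change in anxiety is not a progression criterion, and that response rates will be reported. This limits the consequence. It does not make the weaker analysis preferable when the extra scores are already collected.

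**Conclusion.** The point holds in a limited form. ANCOVA at each follow-up, on its natural reading, leaves the within-group changes open to selective non-response in a study that expects 40% loss. Where loss depends on the 1-month reaction, the modelled error is modest. It could be larger where loss depends on current distress, but there a change of model helps little. The correlations, odds ratios and dropout patterns are all assumed, so these figures illustrate possible size and do not predict it. The planned power is adequate. The change is worth making because the alternative rests on a weaker missingness assumption and corrects error in either direction when observed scores explain the loss.

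**What to change.** Make the primary analysis one linear mixed model for repeated measures per continuous outcome that has a baseline score. Use all available baseline, 1-, 3- and 6-month scores, with time × risk group, the covariates already planned, practice, and an unstructured within-woman covariance. Estimate the change at each time point and the risk-group contrast from that model.

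Keep the per-visit ANCOVA as a sensitivity analysis. Add a delta-based sensitivity analysis that shifts the assumed change in non-responders in both directions and lets the shift differ by risk group, because women with no follow-up score are not recovered beyond what baseline predicts.

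The cost is analysis wording only, since every score is already scheduled for collection. The downside is a slightly more complex model that relies on data being missing at random given the observed scores.
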